### Statistical Methods

For the primary aim, data will be summarized as means  standard deviation. Baseline inflammatory and vascular values will be compared across trials using a one-way ANOVA followed by Tukey’s post-hoc test. A 2-way ANOVA will be used to evaluate potential interactions between Trial 1, 2, and 3, and time of measurement (baseline, immediately post-challenge, 1 hour post-challenge, and 1 day post-challenge). For the secondary aim, baseline values will be compared using a one-way ANOVA. Mean values in pulmonary inflammation, systemic inflammation, and vascular function between the exercise and the resting protocol, challenge or placebo, and time of measurement will be evaluated using a 3-way ANOVA.

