# Patients and Methods

## Study Design

### General Design

This study is a case-control study utilizing a repeated measure design. Each participant will undergo a series of bronchial challenges trials, including

- Mannitol challenge
- Methacholine challenge
- Placebo (control) challenge.

Vascular parameters such as flow mediated dilation (FMD; endothelial function) and pulse wave velocity (PWV; arterial stiffness) will be evaluated before, immediately after, 1 hour after, and 24 hours after each challenge. Blood samples will be obtained for analysis of systemic inflammatory response and exhaled breath condensate will be collected for analysis of pulmonary inflammation and oxidative stress at each time-point.

For the secondary objective, the subjects will in a random order either exercise for 30 minutes or rest for 30 minutes before being subjected to either a placebo challenge or a mannitol challenge, in a cross-over design. The same parameters as for the primary objective will be evaluated before, immediately after, 1 hour after, and 24 hours after each challenge.

1. ***Case-control studies***

*Definition of study groups:*

Asthmatics, defined according to CTS criteria[^22^](#_ENREF_22), will be recruited for the study. This repeated measure design will minimize the risk of between-groups variability and match the case and the control group on all variables except the experimental parameters within the different trails.

*Blinding and avoiding bias:*

All subjects will be blinded to what bronchial challenge is administered. The challenges will be administered in random order and the research staff performing the vascular function analysis will be blinded to what challenge the participant has undergone within each trail.

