## Statistical Plan

### Sample Size Determination

We do not know the anticipated effect of our interventions on FMD; however, based on previous studies[^8^](#_ENREF_8), a total of 20 subjects per group will be sufficient to detect a difference in FMD between trials (α=0.05, power=0.8). An additional 10 subjects per group will be recruited to account for dropouts. Thus, 60 subjects will be recruited for aim 1 and 60 subjects will be recruited for aim 2.

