**2. Material and Supply**

**Asthma Challenges Kits**: Methacholine challenges will be performed on 16 subjects to evaluate the inflammatory and vascular responses to bronchoconstriction. Mannitol challenges will be evaluated on the same 16 subjects during rests and following acute exercise, i.e. a total of 32 mannitol challenges will be conducted.

| Aridol (Mannitol) 32 X $80.14 | $2,564 |
| --- | --- |
| Methacholine 16 X $50.00 | $800 |
| **Total Asthma Challenges Kits** | **$3,364** |

**Exhaled Breath Condensate (EBC)**: EBC will be collected using the RTube™ EBC collector before and 1 and 24 hour following each asthma challenge (4 challenges X 16 subjects X 3 time-points = 192 samples) for analysis of CRP (see attached quote from Eve technologies).

| RTube™ EBC 100 kit (2x) | $6,060 |
| --- | --- |
| EBC analysis (attached quote) CRP (n=192) | $3,720 |
| **Total EBC** | **$9,780** |

**Systemic Inflammatory Markers**: Venous blood will be collected and processed for serum analysis before and 1 and 24 hour following each asthma challenge (4 challenges X 16 subjects X 3 time-points = 192 samples) for analysis of IL-6, TNFα, CRP (see attached quote from Eve technologies). The anti-inflammatory cytokine IL-10 will be analyzed serum before and 1 and 24 hour following the exercise/mannitol challenge (1 challenge X 16 subjects X 3 time-points = 48 samples).

| Blood collection supplies (vacutainers, alcohol wipes, needles) | $500 |
| --- | --- |
| Blood analysis (see attached quote) |  |
| IL-6, TNFα, CRP (n=192 in duplicates (384)) and IL-10 (n=48 in duplicates (96)) | $9,698 |
| **Total Systemic Inflammatory Markers** | **$10,198** |
|  |  |

**Other Supplies**: A CPET will be performed on all participants to determine peak oxygen consumption. Respiratory gas exchange data will be obtained, with oxygen consumption, ventilation, heart rate, rating of perceived exertion and dyspnea recorded. All will perform the test with a 12-lead ECG. These funds are required as all these expendables are needed to do our basic experiments.

| Metabolic Measurement: mouthpieces, mouth filters, ECG electrodes, pulse oximetry electrodes, ultrasound jelly. | $500 |
| --- | --- |
| **Total Other Supplies** | **$500** |

| **Total Material and Supplies** | **$23,842** |
| --- | --- |

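### The design is within-person, but the ANOVAs in Statistical Methods name no participant term; run as named, they use the wrong error term

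*Protocol*

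**What the plan says.** General Design (3.1.1) states: "This study is a case-control study utilizing a repeated measure design". Each participant undergoes mannitol, methacholine and placebo in random order, with vascular measures before, immediately after, 1 hour after and 24 hours after each. Aim 2 crosses exercise or rest with mannitol or placebo in the same people. The section justifies the design by its control of variability between groups.

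Statistical Methods (3.4.2) names three procedures:
- For baselines: "Baseline inflammatory and vascular values will be compared across trials using a one-way ANOVA", followed by Tukey's test.
- For aim 1: "A 2-way ANOVA will be used to evaluate potential interactions between Trial 1, 2, and 3, and time of measurement". Time has four levels, and baseline is one of them.
- For aim 2: a 3-way ANOVA of exercise, challenge and time.

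No participant effect is mentioned in any of them. Sample Size Determination (3.4.1) says that "a total of 20 subjects per group will be sufficient to detect a difference in FMD between trials (α=0.05, power=0.8" and that "An additional 10 subjects per group will be recruited to account for dropouts", although no separate groups exist.

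**The concern.** One-, two- and three-way ANOVA, as ordinarily named, assume independent observations. Here one person supplies up to 12 values in aim 1 and 16 in aim 2, and these are correlated. If participant is left out of the model, the stable differences between people go into the error term, and those are the differences that the design was chosen to remove. The main interaction test then almost never rejects, while other lines of the same ANOVA table can reject too often. An analyst who followed Statistical Methods to the letter would comply with the protocol and still get a wrong primary test.

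**Working it through.** **Structure.** Aim 1: 3 trials × 4 times = 12 values per person; interaction df = (3−1)(4−1) = 6. Aim 2: 2 × 2 × 4 = 16 values; three-way interaction df = 1 × 1 × 3 = 3.

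**The plan's own figure.** The 20 per group cannot be reproduced. The protocol says "We do not know the anticipated effect of our interventions on FMD" and gives no SD or correlation. It can only be back-solved (two-sided α of 0.05 assumed, power 0.80):
- two independent groups: d = √[2(1.960+0.842)²/20] = 0.886 SD;
- paired comparison: mean/SD of differences = 0.66.

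Both fit, so the sample size does not settle which analysis was meant.

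**Error terms.** Write the variances as P (person), S (session within person) and E (residual).

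| Test | Expected mean square under no effect | Denominator as named |
|---|---|---|
| Trial × time | E | P+S+E |
| Trial main effect | E+4S | P+S+E |
| Baseline one-way | S+E | P+S+E |

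**Assumed values** (FMD points, not from the protocol): SDs 2.5, 0.8 and 1.5, so P = 6.25, S = 0.64, E = 2.25, total 9.14.

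*Trial × time, n=20.*
- As named, the F ratio is deflated to 2.25/9.14 = 0.246 of its proper size. The 5% critical value on 6 and 12×19 = 228 df is 2.14. On the correct scale that is 2.14 × 9.14/2.25 ≈ 8.7.
- With participant terms, the error is E on 6×19 = 114 df and the critical value is 2.18.
- Power for an effect of −1.5 in mannitol, immediately post only: noncentrality = n·δ²·(2/3)(3/4)/E = 20 × 2.25 × 0.5/2.25 = 10, which gives 0.62 from the noncentral F.
- Simulation: with participant terms, type I error 0.050 and power 0.61. As named, type I error 0.000 and power 0.003 to 0.004.

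*Trial main effect.* It is too liberal when E+4S > P+S+E, that is, when 3S > P. Under the SDs above, 3 × 0.64 = 1.92 < 6.25, so it is conservative. With variance shares P=0.2, S=0.5, E=0.3, 3S = 1.5 > 0.2. The F ratio is then inflated to about (0.3+2.0)/1 = 2.3, and simulated type I error is 0.28.

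*Baseline one-way ANOVA.* The ratio is (0.64+2.25)/9.14 = 0.32, again too conservative.

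**Other assumptions.** Total variance 1, person share 0.2 to 0.7, session share 0 to 0.5, residual share 0.25 to 0.5, n=20:

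| | As named | With participant terms |
|---|---|---|
| Trial × time, rejection under no effect | 0.000–0.002 | 0.046–0.054 |
| Trial × time, power at 0.886 SD | 0.18–0.33 | 0.84–1.00 |
| Trial main effect, rejection under no effect | 0.00–0.28 | not tabulated |

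Ignoring a within-person correlation ρ overstates the standard error of a within-person difference by 1/√(1−ρ): 1.20 at ρ=0.3 and 2.24 at ρ=0.8. Period effects and non-spherical errors were not simulated.

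**The case against.** The strongest reply is that General Design itself speaks of repeated measures, so repeated-measures ANOVA may simply have been intended, with model detail left to an SAP that is not shown. This stands as far as it goes: under that reading the error term is right. It does not close the point. The protocol does name its tests, and the names, the use of Tukey and the per-group sample size all fit independent groups.

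A reader might infer more than the documents support:

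- *That the 6-df test is itself the cause of low power.* It is not. With participant terms the same test goes from under 1% to about 61%. A single baseline-adjusted mannitol–placebo contrast reaches about 75% under the same assumptions, but only if placed at the time when the effect occurs. Placed at 1 hour for an immediate-only effect, it has 5%. The plan also states that "60 subjects will be recruited for aim 1 and 60 subjects will be recruited for aim 2". If 40 complete aim 1, the figures are 93% and about 97%. Choosing one contrast is a trade-off.
- *That the interaction does not answer the question.* The primary objective covers both pulmonary inflammation and bronchoconstriction. Trial by time, with baseline as a time level, does test whether responses differ by challenge.
- *That anyone missing a session is excluded.* The protocol states no such rule. The 10 extra per group are a recruitment allowance.
- *That the lack of a period term or a log scale for markers is an error.* Those are commonly left to an SAP.

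**Conclusion.** The point holds as a mismatch between General Design and Statistical Methods. Run as named, the ANOVAs use the wrong error term in both aims. With appreciable within-person correlation, the direction for trial by time does not depend on the assumed values: the test is too conservative. The size does depend on them. At n=20 under the SDs above, type I error is about 0% against 5%, and power is under 1% against about 61%. The trial main effect can go either way, up to 0.28 when session-to-session variance is large relative to person variance.

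It would go too far to say that the trial's error estimates are wrong as a matter of fact. That is conditional on the literal reading, and if repeated-measures ANOVA was meant, only the wording is at fault. Because the validity of the primary test turns on this, the protocol should not leave it open.

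**What to change.** Amend Statistical Methods to name a repeated-measures or linear mixed model for both aims:
- random effects: participant and participant-by-session;
- fixed effects: challenge, time and their interaction, with exercise and its interactions added for aim 2;
- all available sessions used.

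Reword Sample Size Determination so that it counts participants who each receive every challenge, not subjects per group.

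As a lesser point, drop the significance tests of baseline across trials. Use each session's baseline as a covariate for the post-challenge values, in which case it leaves the time factor. State in advance which challenge-versus-placebo comparisons and time points follow the interaction test.

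The cost is statistical wording and a standard mixed-model program. No new data are needed.

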# Data Handling and Record Keeping

***Data to be collected:***

**Outcome variables:**

Endothelial function

*Source of the data:* Flow-mediated dilation test (see *measurement, endothelial function* above).

*Time point for collection:* At baseline, immediately after each bronchial challenge, 1 hour after each challenge and at 24 hours after each challenge.

*Who will collect the data:* All data will be collected by trained research staff associated with the study.

*Why the data is being collected:* To evaluate the influence of acute pulmonary inflammation on vascular health, and the influence of exercise on vascular dysfunction following acute inflammation.

*Is the data from a standardized tool:* Yes.

*What form will the data will take (e.g. binary, continuous (numeric), time to event):* Continuous.

Arterial stiffness

*Source of the data:* pulse wave velocity test (see *measurements, arterial stiffness* above).

*Time point for collection:* At baseline, immediately after each bronchial challenge, 1 hour after each challenge, and at 24 hours after each challenge.

*Who will collect the data:* All data will be collected by trained research staff associated with the study.

*Why the data is being collected:* To evaluate the influence of acute pulmonary inflammation on vascular health, and the influence of exercise on vascular dysfunction following acute inflammation.

*Is the data from a standardized tool:* Yes.

*What form will the data will take (e.g. binary, continuous (numeric), time to event):* Continuous.

Systemic inflammation

*Source of the data:* Venous blood samples (see *measurements, systemic inflammation* above).

*Time point for collection:* At baseline, immediately after each bronchial challenge, 1 hour after each challenge, and at 24 hours after each challenge.

*Who will collect the data:* All data will be collected by trained research staff associated with the study.

*Why the data is being collected:* To evaluate changes in systemic inflammatory levels throughout the study protocol.

*Is the data from a standardized tool:* Yes.

*What form will the data will take (e.g. binary, continuous (numeric), time to event):* Continuous.

Pulmonary inflammation

*Source of the data:* Exhaled breath condensate (see *measurements, pulmonary inflammation* above).

*Time point for collection:* At baseline, immediately after each bronchial challenge, 1 hour after each challenge, and at 24 hours after each challenge.

*Who will collect the data:* All data will be collected by trained research staff associated with the study.

*Why the data is being collected:* To evaluate changes in pulmonary inflammatory levels throughout the study protocol.

*Is the data from a standardized tool:* Yes.

*What form will the data will take (e.g. binary, continuous (numeric), time to event):* Continuous.

**Explanatory variables and potential cofounding variables:**

Subject demographics

*Source of the data:* interview with subject.

*Time point for collection:* during a pre-test session.

*Who will collect the data:* All data will be collected by trained research staff associated with the study.

*Why the data is being collected:* To ensure subject meet the inclusion/exclusion requirements, and to obtain general sample characteristics.

*Is the data from a standardized tool:* No, subject demographics will be collected according to

*What form will the data will take (e.g. binary, continuous (numeric), time to event):* Nominal or ordinal.

Perceived level of control

*Source of the data:* The asthma control questionnaire .

*Time point for collection:* during a pre-test session, and at each baseline time-point.

*Who will collect the data:* All data will be collected by trained research staff associated with the study.

*Why the data is being collected:* To evaluate the current levels of perceived asthma control at each study day.

*Is the data from a standardized tool:* Yes.

*What form will the data will take (e.g. binary, continuous (numeric), time to event):* Continuous.

Lung function

*Source of the data:* Pulmonary function test (see *measurements, pulmonary function* above)

*Time point for collection:* during a pre-test session, and at each baseline time-point.

*Who will collect the data:* All data will be collected by trained research staff associated with the study.

*Why the data is being collected:* To evaluate baseline lung function at each study day.

*Is the data from a standardized tool:* Yes.

*What form will the data will take (e.g. binary, continuous (numeric), time to event):* Continuous.

Data collection forms and questionnaires are included as appendices.

## Confidentiality

Each research participant will be assigned a study ID which will not be associated with any personal identifiable information. All collected study data will be stored either on password protected computer hard drives or in locked filing cabinets.

## Records Retention

All data will be stored for 5 years following the completion of the study, whereby it will be destroyed.

## Regulatory Binder

The investigator will maintain a regulatory binder containing all information pertinent to the study.

# Study Auditing and Inspecting

Not applicable.

# Budget

Source of Funding: This study will be funded by [name] operating grant.

For complete budget, please see appendix 1.

Budget summary:

| Salaries and Benefits | | $14,985 |
| --- | --- | --- |
| Materials and Supplies | | $23,842 |
| Payment to Subjects | | $4,096 |
| Publications | | $2,000 |
| **TOTAL BUDGET** | **$44,923** | |
|  |  | |

# Publication Plan

Upon completion, this study is expected to be published as two separate peer-reviewed research articles.

# Attachments

Appendix 1. Budget

**1. Salaries and Benefits**

**Research Assistant**: Funds are requested for the salary one research assistant (0.25 full-time equivalents, FTE). This person will assist with data collection for all aims and ensure quality control of all data collection and data analysis.

| FTE | 1.0 | 0.25 |
| --- | --- | --- |
| Salary (Grade 6, Step 5): | $46,155 | $11,539 |
| Benefits (23%): | $13,786 | $3,447 |
| **Total Salaries and Benefits** |  | **$14,985** |

**2. Material and Supply**

**Asthma Challenges Kits**: Methacholine challenges will be performed on 16 subjects to evaluate the inflammatory and vascular responses to bronchoconstriction. Mannitol challenges will be evaluated on the same 16 subjects during rests and following acute exercise, i.e. a total of 32 mannitol challenges will be conducted.

| Aridol (Mannitol) 32 X $80.14 | $2,564 |
| --- | --- |
| Methacholine 16 X $50.00 | $800 |
| **Total Asthma Challenges Kits** | **$3,364** |

**Exhaled Breath Condensate (EBC)**: EBC will be collected using the RTube™ EBC collector before and 1 and 24 hour following each asthma challenge (4 challenges X 16 subjects X 3 time-points = 192 samples) for analysis of CRP (see attached quote from Eve technologies).

| RTube™ EBC 100 kit (2x) | $6,060 |
| --- | --- |
| EBC analysis (attached quote) CRP (n=192) | $3,720 |
| **Total EBC** | **$9,780** |

**Systemic Inflammatory Markers**: Venous blood will be collected and processed for serum analysis before and 1 and 24 hour following each asthma challenge (4 challenges X 16 subjects X 3 time-points = 192 samples) for analysis of IL-6, TNFα, CRP (see attached quote from Eve technologies). The anti-inflammatory cytokine IL-10 will be analyzed serum before and 1 and 24 hour following the exercise/mannitol challenge (1 challenge X 16 subjects X 3 time-points = 48 samples).

| Blood collection supplies (vacutainers, alcohol wipes, needles) | $500 |
| --- | --- |
| Blood analysis (see attached quote) |  |
| IL-6, TNFα, CRP (n=192 in duplicates (384)) and IL-10 (n=48 in duplicates (96)) | $9,698 |
| **Total Systemic Inflammatory Markers** | **$10,198** |
|  |  |

**Other Supplies**: A CPET will be performed on all participants to determine peak oxygen consumption. Respiratory gas exchange data will be obtained, with oxygen consumption, ventilation, heart rate, rating of perceived exertion and dyspnea recorded. All will perform the test with a 12-lead ECG. These funds are required as all these expendables are needed to do our basic experiments.

| Metabolic Measurement: mouthpieces, mouth filters, ECG electrodes, pulse oximetry electrodes, ultrasound jelly. | $500 |
| --- | --- |
| **Total Other Supplies** | **$500** |

| **Total Material and Supplies** | **$23,842** |
| --- | --- |

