***Secondary Objective***

To evaluate the influence of *acute* exercise on systemic inflammatory and vascular responses to acute pulmonary inflammation.

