*Mannitol challenge -* The mannitol challenge will be conducted according to the protocol created and validated to the methacholine challenge by the inventor[^32^](#_ENREF_32); dry powder mannitol (Aridol®, Pharmaxis Inc., Exton, PA, USA) will be inhaled in concentrations of 0, 5, 10, 20, 40, 80, 160, 160 and 160 mg mannitol, for a total cumulative dose of 653 mg. Spirometry, as described previously, will be performed before the first inhalation to receive baseline lung function values, and at 1 minute following each of the doses. The value for FEV_1_ following the inhalation of 0 mg mannitol will be the reference value used for comparison for the remainder of the challenge. The challenge will be considered positive if a cumulative concentration of ≤ 635 mg mannitol yield a reduction in FEV_1_ of ≥ 15% compared to baseline (0 mg mannitol) FEV_1_ (PD_15_; provocative dose yielding a 15% reduction in FEV_1_) whereby the challenge will end. A cumulative dose of 635 mg will be used as the maximum dose for when/if a mannitol challenge does not resulted in a ≥15% reduction in FEV_1_ (negative tests).

As shown previously[^32^](#_ENREF_32), the FEV_1_ will in most people spontaneous recovery to within 95% of baseline values within 60 minutes following the last mannitol inhalation and reliever medication will not be required. Capillary oxygen saturation will be monitored throughout the challenge (Radical 7, Masimo, Neuchatel, Switzerland), including the recovery, and the FEV_1_ will be measured every 10 minutes following the last inhalation of mannitol until the FEV_1_ has returned to within 95% of baseline values. In case of an unexpected severe bronchoconstriction following the last inhalation of mannitol, the subject will be given 400 mg Salbutamol (Ventolin® inhaler)[^32^](#_ENREF_32) to relax the airways. A physician will be available for supervision of all mannitol challenges.

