**3. Payment to Study Subjects**

**Parking and Honoraria**: All research participants will be reimbursed for parking at the University of Alberta East Parkade (4 challenges X 2 days X 16 participants = 128 visits). Participants who complete all parts of the study will receive a $200 gift card (on average - $25/visit) at their choice.

| Parking ($7/day) | $896 | |
| --- | --- | --- |
| Honoraria ($200/subject) | $3,200 | |
| **Total Payment to Subjects** | | **$4,096** |

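### Aim 2's 3-way ANOVA needs a placebo session after exercise as well as after rest, but Appendix 1 counts only one placebo per subject

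*Protocol*

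**What the plan says.** **Body of the protocol.** The Secondary Objective is to evaluate the influence of acute "exercise on systemic inflammatory and vascular responses to acute pulmonary inflammation". Section 3.1.1 (General Design) has subjects, in random order and in a cross-over, "either exercise for 30 minutes or rest for 30 minutes before being subjected to either a placebo challenge or a mannitol challenge". Section 3.4.2 (Statistical Methods) says that mean values "between the exercise and the resting protocol, challenge or placebo, and time of measurement will be evaluated using a 3-way ANOVA". These three places agree with each other and describe a full crossing of condition (exercise or rest) with challenge (mannitol or placebo).

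**Appendix 1, Material and Supply.** "Methacholine challenges will be performed on 16 subjects", and "Mannitol challenges will be evaluated on the same 16 subjects during rests and following acute exercise", 32 mannitol challenges in all. Breath condensate and blood samples are both counted as "4 challenges X 16 subjects X 3 time-points = 192 samples".

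**Appendix 1, Payment to Study Subjects.** Parking is counted as "4 challenges X 2 days X 16 participants = 128 visits", and the $200 honorarium is put at $25 per visit on average, which is 8 visits or four challenges of two days each.

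The only exercise session that Appendix 1 names is the one with mannitol, in the IL-10 line. No placebo session after exercise is named.

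**The concern.** Whether exercise changes the response to a challenge is an interaction question. It needs the mannitol-minus-placebo difference after exercise and the same difference after rest, so four sessions. Appendix 1 leaves room for three of them once methacholine is counted. If its schedule is the one run, the planned 3-way ANOVA cannot be fitted with the terms that answer the secondary objective.

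The comparison that remains, mannitol after exercise against mannitol after rest, cannot by itself tell a direct effect of exercise on FMD or on the inflammatory markers from a changed response to mannitol. The breath condensate markers do not help, because they too would lack a placebo session after exercise. No later analysis plan can recover a cell that was never collected, so this has to be settled before sessions are run.

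**Working it through.** **1. Appendix 1's own counts reproduce.**
- Samples: 4 × 16 × 3 = 192.
- Visits: 4 × 2 × 16 = 128.
- Parking and honoraria: 128 × $7 = $896; 16 × $200 = $3,200; total $4,096.
- Honorarium per visit: $200 / 8 = $25.

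All agree on four challenges per subject.

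**2. What the four challenges are.**
- Mannitol: 32 / 16 = 2 per subject (rest, and after exercise).
- Methacholine: 16 / 16 = 1 per subject.
- Remainder: 4 − 2 − 1 = 1 per subject.

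Appendix 1 does not name the remaining challenge. General Design lists only mannitol, methacholine and placebo, so by subtraction it is the placebo.

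**3. What the body needs.** Aim 2 needs rest+placebo, rest+mannitol, exercise+placebo and exercise+mannitol. Aim 1 needs methacholine, mannitol and placebo. At 16 subjects:
- Same subjects in both aims, rest sessions shared: 5 sessions each, 5 × 2 × 16 = 160 visits.
- Same subjects, nothing shared: 4 + 3 = 7 sessions each, 7 × 2 × 16 = 224 visits.
- Separate Aim 2 sample: 4 sessions per Aim 2 subject, without methacholine.

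**4. Estimability with one placebo.** With four time-points the full model has 16 parameters:

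| Term | df |
| --- | --- |
| Intercept | 1 |
| Exercise | 1 |
| Challenge | 1 |
| Time | 3 |
| Exercise × time | 3 |
| Challenge × time | 3 |
| Exercise × challenge | 1 |
| Exercise × challenge × time | 3 |

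Three sessions at four times give 3 × 4 = 12 cell means, so the rank is 12. The first six terms already use 1 + 1 + 1 + 3 + 3 + 3 = 12, which leaves 0 df for the last two (16 − 12 = 4 df lost). With subject intercepts for 16 subjects the rank is 27 of 31 columns at four time-points, and 24 of 27 at Appendix 1's three. With all four cells it is 31 of 31 and 27 of 27. The result is the same whether the single placebo follows rest or exercise. If it follows exercise, Aim 1 also loses its resting control.

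**5. What the remaining contrast measures.** Write E or R for exercise or rest, and M or P for mannitol or placebo:

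EM − RM = (EP − RP) + [(EM − EP) − (RM − RP)]

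The first term is exercise's own effect. The bracket is the altered response that the secondary objective asks about. Without both EP and RP the two cannot be separated.

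**6. Illustration only.** Assume no altered response, and an own effect of exercise on the change score of 0.25, 0.5 or 0.75 SD of the within-person difference between sessions. A paired t-test of EM against RM (two-sided 0.05, noncentrality d√n) with 16 subjects is significant in 15.5%, 46.5% or 80.1% of trials. The four-cell interaction test stays at about 5%. If exercise has no own effect, both are 5%. The protocol gives no figure for this effect.

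**The case against.** The strongest reply is that no analysis choice is faulty. Read alone, General Design and Statistical Methods imply all four cells and a model of full rank. The contrary source is a budget, and it departs from the body elsewhere: 16 subjects against 60 per aim, three time-points against four, IL-10 added, IL-8 and 8-isoprostane absent. It may describe a smaller or different plan. This stands, and it makes the estimability problem conditional on the Appendix 1 schedule. It does not remove the contradiction: the appendix is part of the protocol, nothing says which text governs, and the visit count affects FMD as well as the assays.

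Second, five sessions per subject is not a requirement of the body. Sample Size Determination gives 60 subjects for each aim without saying that they are the same people. With a separate Aim 2 sample, four sessions suffice. This stands for the body. It does not rescue Appendix 1, which puts methacholine and both mannitol challenges on the same 16 subjects.

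Third, a reader might infer that nothing in the data could reveal a direct effect of exercise. That goes too far. General Design measures before each challenge but does not say whether this is before or after the exercise. If it is after, an immediate effect would show at baseline, where Statistical Methods compares conditions. An effect that emerges or changes later would still be confounded.

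A reader might also add that mannitol is titrated in each session ("provocative dose yielding a 15% reduction in FEV_1_) whereby the challenge will end"). Titration would be the same with all four cells, so it is no part of this point.

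**Conclusion.** The contradiction between the body and Appendix 1 on sessions per subject is real, and the counts and ranks follow from the document alone, given that the unnamed fourth challenge is the placebo.

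- If Appendix 1 governs, exercise × challenge and exercise × challenge × time have no degrees of freedom, and the 3-way ANOVA cannot be run as written.
- If the body governs and the same subjects serve both aims, Appendix 1 is one session per subject short with shared rest sessions (32 visits at 16 subjects), and three short without sharing.

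Two stronger readings are not supported. One is that the protocol's analysis cannot answer the secondary objective at all; that holds only under the Appendix 1 schedule. The other is that the trial has a false-positive rate of the size illustrated; those percentages rest on assumed effects. The point concerns the secondary objective and should be corrected before sessions are run. The difference in subject numbers is a separate matter.

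**What to change.** **Preferred.** In General Design, list the four Aim 2 sessions (rest+placebo, rest+mannitol, exercise+placebo, exercise+mannitol) and state whether the same subjects and rest sessions also serve Aim 1. Correct the Appendix 1 counts to match. Keep the 3-way ANOVA and name exercise × challenge × time as the term for the secondary objective.

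Cost of a fifth session for 16 subjects at the protocol's own prices (32 visits, 16 × 3 = 48 samples):
- Parking: 32 × $7 = $224.
- Honoraria: 32 × $25 = $800, if the per-visit rate is kept.
- Breath condensate assays: 48 × $3,720 / 192 = $930.
- Collectors: 48 × $30.30 = $1,454 (taking $6,060 as the price of 200), or $3,030 for one further kit. Any spares from the first 200 reduce the per-unit figure.
- Blood assays: at most a quarter of $9,698, or $2,425.

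The total is about $5,833 to $7,409, or 13.0% to 16.5% of $44,923, without staff time. No extra mannitol kit is needed. The other costs are two more visits per subject and a noisier estimate. With independent session errors the interaction's SD is √2 times larger, so with 16 subjects 80% power needs 1.06 SD, against 0.75 SD for the simple mannitol contrast (0.93 against 0.66 with 20).

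**Alternative that keeps four sessions and the 3-way ANOVA.** Use a separate Aim 2 sample without methacholine. This needs more subjects.

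**If only four challenges per subject, including methacholine, will be run.** Replace the 3-way ANOVA with a 2-way analysis (mannitol after exercise or rest, by time) and word the Aim 2 conclusion as the total effect of exercise before a mannitol challenge. This costs only text, but gives up the claim that exercise alters the response.
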